#### Rescue treatment

Patients who do not respond rapidly to treatment will be administered rescue medication. If a patient vomits twice, he or she will receive parenteral therapy with artesunate and will be withdrawn from the study. Patients with signs of severe or complicated malaria will be hospitalised and treated with parenteral therapy and relevant supportive treatment. If a patient meets one of the criteria for therapeutic failure, he or she will be treated according to current national recommendations.

### Strategies to improve adherence to interventions {11c}

Patients of both arms will be visited at home by study staff on alternate days and provided with medication for 2 days. On the day of visit, primaquine doses will be observed and the patient is advised to take treatment on the following day. The patient will also be asked about the previous day’s dose. If patients are not found/located, all efforts will be made to ensure that they restart treatment.

### Relevant concomitant care permitted or prohibited during the trial {11d}

At enrolment, all anti-malarial medications received in the preceding 28 days will be documented on the clinical record form (CRF). Regular medication at trial entry for conditions other than malaria will be documented. Patients will be asked to continue to take any regular medications in their usual prescriptive way. Additional drugs taken during the trial period for whatever reason will be documented. Patients discontinuing their trial medication prematurely, or who fail to respond to trial medication and receive other anti-malarial therapy, will be recorded with a start and end date. Intake of drugs with antimalarial activity will be discouraged, unless prescribed by the medical officer of the trial.

### Provisions for post-trial care {30}

The sponsor has a provision of insurance, which is in accordance with the legal requirements. This insurance provides coverage for damage to research subjects through injury or death caused by any activities of the study.

### Outcomes {12}

#### Primary outcomes

##### Efficacy

The incidence risk of symptomatic *P. vivax* malaria at 6 months.A participant will be considered to have demonstrated recurrence-free efficacy at 6 months if:The participant had *P. vivax* asexual parasitaemia at enrolment.The participant has initial clearance of *P. vivax* parasitaemia defined as two negative blood films for asexual P. vivax parasites, with at least 6 h between the counts, and no positive blood films in the interval.The participant was aparasitaemic for asexual *P. vivax* at any assessment following initial parasite clearance.The participant did not take a concomitant medication with anti-malarial activity at any point between the initial study day and their last parasite assessment.The participant is parasite-free at the end of 6 months.

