**Methods:**

This is a hospital-based, randomised, controlled, open-label trial in two centres in India. Patients above the age of 16 years, with uncomplicated vivax malaria, G6PD activity of ≥ 30% of the adjusted male median (AMM) and haemoglobin levels ≥ 8 g/dL will be recruited into the study and randomised in a 1:1 ratio to receive standard schizonticidal treatment plus 7-day primaquine at 0.50 mg/kg/day or standard care with schizonticidal treatment plus 14-day primaquine at 0.25 mg/kg/day. Patients will be followed up for 6 months. The primary endpoint is the incidence risk of any *P. vivax* parasitaemia at 6 months. Safety outcomes include the incidence risk of severe anaemia (haemoglobin < 8 g/dL), the risk of blood transfusion, a > 25% fall in haemoglobin and an acute drop in haemoglobin of > 5 g/dL during primaquine treatment.

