### Objectives {7}

To assess the 6-month efficacy of a 7-day course of primaquine treatment regimen (0.50 mg/kg/day) in preventing recurrent *P. vivax* parasitaemia in G6PD normal patients over 16 years of age compared to the current 14-day primaquine regimen (0.25 mg/kg/day)To assess the safety and tolerability of a 7-day course of primaquine treatment regimen compared to the current standard primaquine regimen.

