#### Secondary efficacy outcome

The incidence risk of any (symptomatic and asymptomatic) *P. vivax* malaria at day 28 and at 6 months.

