## Statistical methods

### Statistical methods for primary and secondary outcomes {20a}

#### Efficacy analyses

The efficacy analyses will be based on the modified intention to treat population. Time to first recurrent vivax parasitaemia will be used to compute the Kaplan-Meier estimates of risk of *P. vivax* recurrence at month 6 for treatment arms and control arms with primaquine for each study site. Also, the comparison of the relative hazards between trial arms (hazard ratio (95% confidence interval)) will be estimated from a Cox regression model for the time to the first recurrent episode.

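### The primary efficacy endpoint is symptomatic vivax malaria in the outcomes section but any vivax parasitaemia in the abstract, and the latter is also listed as secondary

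*Protocol article*

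**What the plan says.** Five places in the protocol article define the efficacy event, all but one at 6 months.

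- **Outcomes {12}, primary efficacy outcome:** "The incidence risk of symptomatic *P. vivax* malaria" at 6 months. The criteria listed under it for recurrence-free efficacy concern parasites and concomitant antimalarials only: initial clearance, no asexual parasites at later assessments, parasite-free at the end of follow-up. None mentions fever or symptoms.
- **Abstract, Methods:** "The primary endpoint is the incidence risk of any *P. vivax* parasitaemia at 6 months".
- **Secondary efficacy outcome:** "The incidence risk of any (symptomatic and asymptomatic) *P. vivax* malaria at day 28 and at 6 months".
- **Objectives {7}:** efficacy "in preventing recurrent *P. vivax* parasitaemia", with no symptom limit.
- **Statistical methods {20a}, Efficacy analyses:** "Time to first recurrent vivax parasitaemia will be used to compute the Kaplan-Meier estimates", followed by a Cox model for the first recurrent episode. This is the only efficacy variable described there, and it has no symptom limit.

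Trial design {8} states a non-inferiority, open-label trial. Sample size {14} uses a control recurrence rate of about 13%, a margin of 10%, 200 per group, 30% loss, 5% significance and 68% power. It does not say whether the 13% counts symptomatic recurrences or all recurrences.

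**The concern.** Any vivax infection at 6 months is primary in the abstract and secondary in the outcomes section. The outcomes section is also inconsistent within itself: a participant without symptoms whose month 3 slide is positive fails the listed criteria but has no event under the headline above them.

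The difference is practical. Table 1 and the study procedures schedule microscopy on days 7, 14, 21 and 28 and monthly to month 6, whether or not the participant is ill, so recurrences without symptoms can be found.

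Three things are at stake. First, either definition could be reported as the prespecified primary once results are known. Second, symptomatic status rests partly on patient report, and neither patients nor staff are blinded ({17a}), whereas slide positivity is less exposed to that. Third, the event rate determines both the power and how strict a fixed 10-point margin is relative to the control risk.

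**Working it through.** **Inputs from the article.** Control recurrence 13%; margin 10%; 200 per group; 30% loss, so 200 × (1 − 0.30) = 140 evaluable per arm; 5% significance; stated power 68% (all Sample size {14}).

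**Assumptions.** The margin is in absolute percentage points. The test is one-sided at 2.5% (two-sided 5%). The true risks are equal in the two arms. The symptomatic share of recurrences is 60–90%, since the documents give no figure.

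**1. The stated power.** The Farrington–Manning score test at 13%, margin 0.10 and 140 per arm gives 67.7%, which reproduces 68%. The simpler Wald formula is

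power = Φ(0.10 / √(2p(1−p)/140) − 1.96).

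At p = 0.13: √(2 × 0.13 × 0.87/140) = 0.0402; 0.10/0.0402 − 1.96 = 0.53; power 70.1%. The Wald results below therefore start about two points above the article's figure.

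**2. If 13% is any recurrence and the primary is symptomatic malaria** (p = 0.13 × share):

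| Symptomatic share | p | Wald power | Margin ÷ control rate |
|---|---|---|---|
| 100% (reference) | 13.0% | 70.1% | 0.10/0.130 = 77% |
| 90% | 11.7% | 74.0% | 0.10/0.117 = 85% |
| 60% | 7.8% | 87.7% | 0.10/0.078 = 128% |

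Farrington–Manning gives 82.9% at 7.8%: the same direction, with a smaller rise.

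**3. If 13% is the symptomatic rate and the primary is any parasitaemia** (p = 0.13 / share):

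| Symptomatic share | p | Wald power |
|---|---|---|
| 90% | 14.4% | 66.3% |
| 60% | 21.7% | 52.8% |

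**4. Reading the definitions together.** The abstract, the objective, the criteria under the primary headline and the analysis variable all point to parasitaemia regardless of symptoms. The primary headline, and the listing of the all-recurrence outcome as secondary, point the other way. The secondary outcome explicitly includes infections without symptoms, so the word symptomatic in the primary headline cannot be read as a loose synonym for recurrence.

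**The case against.** The contradiction cannot be put down to condensation or to an unseen analysis plan, because the article itself states two different primary endpoints. The objections that carry weight concern what follows from it.

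- **Intent.** A reader might infer that any parasitaemia is plainly the intended primary and that the outcomes headline is a slip. The documents do not settle this. The primary and secondary headlines in Outcomes {12} form a deliberate-looking pair, one symptomatic and one covering all infections. The word any appears in the primary endpoint only in the abstract; the objective and analysis say recurrent parasitaemia without qualification, and the analysis section does not label its variable primary. This objection stands.
- **Timing.** Trial status gives a recruitment start of 11/9/23 and an expected end in March 2024. If the approved protocol names symptomatic malaria, replacing it now would change the primary outcome of a running open-label trial, which is more than a wording edit. This also stands.
- **Type I error.** A reader might infer that a choice between two endpoints raises the one-sided error from 2.5% to as much as 5%. That is a generic bound for two tests. These endpoints are nested and correlated, and the inflation depends on the true risks and on how the choice is made, none of which the documents give. No figure is claimed here.
- **Subjectivity.** Slides are labelled anonymously and read by two independent microscopists, and temperature is taken at follow-up visits. This limits the scope for biased ascertainment of symptoms but does not remove it.
- **Stated power.** The gap between 70% and 68% is a difference of formula and not an error in the article.

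**Conclusion.** The article contradicts itself on its primary efficacy endpoint, and this needs correcting whatever the symptomatic share turns out to be. The contradiction rests on the text alone.

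Its numerical size depends on the assumed 60–90% share and on which event the 13% describes. The effect can run in either direction. With a symptomatic primary and 13% as any recurrence, power is about 88–74% and the margin equals 128–85% of the control rate instead of 77%. With an any-parasitaemia primary and 13% as the symptomatic rate, power is about 66–53%. The documents do not show which endpoint was approved before recruitment, nor that any endpoint has been switched in response to data.

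**What to change.** Before any comparison by arm, name one primary event and use it in the abstract, Objectives {7}, both parts of Outcomes {12}, Sample size {14} and Statistical methods {20a}.

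- Microscopically confirmed *P. vivax* parasitaemia by month 6, with or without symptoms, best fits the abstract, the objective, the listed criteria and the analysis. Symptomatic malaria at 6 months would then become secondary, and all recurrences at day 28 would stay secondary.
- If the protocol approved before recruitment names symptomatic malaria, restore that endpoint instead and align the criteria, abstract and analysis with it.
- Document which endpoint was prespecified and when. State which definition the 13% refers to, restate the power if it changes, and update the registry, as section {25} commits the trial to do.

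No new data are needed: scheduled slides, follow-up temperatures and the symptom questionnaire at unscheduled visits are already collected. The cost is a check of the approved protocol, an amendment and a registry update. Waiting until database lock would be too late, because unblinded staff see outcomes well before then.

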#### Secondary efficacy outcome

The incidence risk of any (symptomatic and asymptomatic) *P. vivax* malaria at day 28 and at 6 months.

##### Safety

The proportion of patients vomiting their medication within 1 hour of administration.The proportion of adverse events and serious adverse events.The incidence risk of anaemia (Hb < 8 g/dL) and/or the risk for blood transfusion.Risk of > 25% fall in haemoglobin on any day of treatment.The incidence risk of an acute drop in Hb of > 5 g/dL during primaquine treatment.Gastrointestinal (GI) tolerability — incidence of abdominal pain, heartburn, diarrhoea, constipation, nausea and vomiting.

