#### Heamoglobin

Haemoglobin will be measured using a point of care using a Hemocue™, which will be used according to manufacturer instructions. This will be done on days 0, 1, 2, 7, 14, 21, and 28 and monthly till month 6 and the day of recurrence.

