#### Safety analysis

All safety endpoints will be based on the safety population and presented in tabular and/or graphical format and summarised descriptively.

Clinical laboratory data (clinical chemistry and haematology) will be summarised by the mean, median, standard deviation, minimum and maximum values by treatment group and time point. Laboratory data will also be evaluated by tabulating the number and percentage of subjects in each treatment group with values outside specified threshold values of clinical concern (these may include values outside of the normal range, outer range of clinical concern, and other values of clinical concern).

AE reporting will be performed using the MedDRA (Medical Dictionaries for Regulatory Activities) coding system. Each AE coded using the MedDRA system can be associated with more than one system organ class (SOC). However, for reporting purposes, an AE will be associated with the primary system organ class only. Counting of AEs will be based on the number of subjects — not the number of AEs. For example, if a subject reports the same AE on three occasions within a time interval, that AE will only be counted only once. Subjects reporting more than one AE in a system organ class will only be counted once in that system organ class total. AEs considered by the investigator to have a reasonable possibility of being related to treatment (drug-related AEs) will be summarised by preferred term and SOC. AEs leading to premature withdrawal from treatment and or study will be summarised by preferred term and SOC. AEs that are considered to be gastro-intestinal-related (i.e abdominal pain, heartburn, diarrhoea, constipation, nausea and vomiting) will be summarised. AEs that are considered to be haematologically related (i.e clinically relevant drops in haemoglobin or haematocrit or other complications) will be summarised. Serious adverse events will be summarised by preferred term and SOC. All safety data relating to vital sign variables will be presented as summary statistics (including number, mean, median, interquartile range, standard deviation, minimum and maximum).

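### Every named haemoglobin outcome is a yes/no cut-off with no between-arm estimate of haemoglobin loss planned, and two of the cut-offs run over unequal windows in the two arms

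*Protocol article*

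**What the plan says.** The Safety list under Outcomes {12} names three haemoglobin outcomes, all yes/no:

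- "The incidence risk of anaemia (Hb < 8 g/dL) and/or the risk for blood transfusion"
- "Risk of > 25% fall in haemoglobin on any day of treatment"
- "The incidence risk of an acute drop in Hb of > 5 g/dL during primaquine treatment"

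No change from baseline and no lowest value is named as an outcome.

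The haemoglobin section of the protocol article sets one Hemocue schedule for everyone: "This will be done on days 0, 1, 2, 7, 14, 21, and 28 and monthly till month 6 and the day of recurrence". Table 1 agrees. It also shows primaquine on days 0-6 in the 7-day arm and days 0-13 in the 14-day arm. A full blood count is scheduled only on day 0 and at recurrence.

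Under Safety analysis, safety endpoints are to be "presented in tabular and/or graphical format and summarised descriptively". Laboratory data, haematology included, "will be summarised by the mean, median, standard deviation, minimum and maximum values by treatment group and time point", with counts of patients beyond thresholds of clinical concern. There is one further item: "AEs that are considered to be haematologically related (i.e clinically relevant drops in haemoglobin or haematocrit or other complications) will be summarised". No difference between arms, with or without an interval, is stated for any safety outcome.

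**The concern.** Both arms receive 3.5 mg/kg in total. What differs is the rate: 0.50 against 0.25 mg/kg/day. Whether the faster rate costs more haemoglobin is therefore a central safety question, and the second objective is to assess safety against the standard regimen.

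The plan has two weaknesses here.

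1. **Information is lost.** Each patient has a day-0 value and later values from the same device on the same days, but the named outcomes keep only whether a threshold was crossed. A moderate loss shared by many patients moves few of them over a threshold. Few crossings in each arm could then be taken for reassurance that the data do not give.
2. **The windows differ.** Two of the cut-offs are tied to days of treatment, and treatment lasts twice as long in the control arm. The arm with the higher daily dose gets fewer chances to show an event.

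**Working it through.** **The plan's own figures.** The protocol gives no expected rate, SD or power for haemoglobin. Its only power figure, 68%, concerns recurrence (with 200 × 0.7 = 140 per arm, one-sided 2.5% and restricted variance it reproduces as 67.7%) and has no bearing on this point.

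**Windows, from Table 1 and the haemoglobin schedule.** Post-baseline readings fall on days 1, 2, 7, 14, 21 and 28.

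| | 7-day arm | 14-day arm |
|---|---|---|
| Dosing days | 0-6 | 0-13 |
| Post-baseline readings on dosing days | 1, 2 | 1, 2, 7 |
| Post-baseline readings on days 1-14 | 1, 2, 7, 14 | 1, 2, 7, 14 |

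Read literally, the > 25% and > 5 g/dL outcomes use two readings in one arm and three in the other. The 7-day arm's value taken the day after its last dose is left out.

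**Sensitivity. Assumed inputs, none of them in the protocol:** 190 per arm with a day-7 value (of 200 randomised), baseline 12.5 g/dL, mean fall 0.5 g/dL in control, SD of change 1.0-1.5 g/dL, normal change, two-sided 5%, extra fall in the 7-day arm 0.3 or 0.5 g/dL.

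*> 25% cut-off.* 25% of 12.5 is 3.125 g/dL. The proportion crossing is 1 − Φ((3.125 − mean fall)/SD).

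- Control, SD 1.0: (3.125 − 0.5)/1.0 = 2.625, giving 0.4%. SD 1.5: 2.625/1.5 = 1.75, giving 4.0%.
- 7-day arm with 0.5 g/dL extra, SD 1.0: 2.125, giving 1.7%. SD 1.5: 2.125/1.5 = 1.417, giving 7.8%.
- Two-proportion power for 0.5 g/dL: 22% (SD 1.0) to 35% (SD 1.5). For 0.3 g/dL: 10% to 15%.

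*> 5 g/dL cut-off.* In the worst case, (5 − 1.0)/1.5 = 2.67, giving 0.4%, or less than one patient in 190.

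*Mean change.* SE = SD × √(2/190), which is 0.103 (SD 1.0) to 0.154 (SD 1.5) g/dL. The 95% CI half-width is 1.96 × SE = 0.20 to 0.30 g/dL. Power is Φ(difference/SE − 1.96).

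- 0.5 g/dL: 0.5/0.1026 = 4.87, power 99.8% (SD 1.0). 0.5/0.1539 = 3.25, power 90% (SD 1.5).
- 0.3 g/dL: power 83% (SD 1.0) to 50% (SD 1.5).

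**Does the ranking depend on the inputs?** A grid of 54 scenarios was run at 190 per arm: baseline 11, 12.5 or 13; control fall 0.5, 1.0 or 1.5; SD 1.0, 1.2 or 1.5; extra fall 0.3 or 0.5 g/dL. Power for the > 25% cut-off was 8-46% for 0.3 g/dL and 18-89% for 0.5 g/dL. For the > 5 g/dL cut-off it never exceeded 17%. The mean had more power than either cut-off in all 54. Under a common shift the ranking is stable, but the gap ranges from very large to small.

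**When the shift is not common.** Suppose instead that a few patients in the 7-day arm lose an extra 4 g/dL (same baseline, control fall and SD range).

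| Share affected | Mean shift | Power, mean | Power, > 25% cut-off |
|---|---|---|---|
| 3% | 0.03 × 4 = 0.12 g/dL | 11-18% | 18-52% |
| 5% | 0.05 × 4 = 0.20 g/dL | 22-38% | 36-78% |

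Here the cut-off does better.

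**The case against.** Four arguments deserve weight.

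- **Haemoglobin is not judged by the cut-offs alone.** A reader might infer that the trial cannot tell whether the higher daily dose costs more haemoglobin. The document does not support that. Means and SDs by arm and day are planned, so anyone could form a crude difference, to about ±0.2-0.3 g/dL on the inputs above. Haematological adverse events are summarised as well. This stands. What is absent is a stated, baseline-adjusted comparison.
- **The cut-offs need not be rare.** A reader might also infer that almost nobody will cross them. The protocol gives no rates. Entry is allowed from 8 g/dL, the anaemia threshold itself, and from G6PD activity of 30% of the adjusted male median. With other plausible inputs, crossings of > 25% ranged from 0.3% to 31%. The single-day calculation also understates an outcome defined over any treatment day: with three correlated readings (assumed r 0.5-0.7) the control rate is about 1.0-1.2% instead of 0.4% (SD 1.0), and 8-10% instead of 4.0% (SD 1.5). This stands too. Rarity is secure only for the > 5 g/dL drop, and no rate for Hb < 8 g/dL was derived.
- **Thresholds aimed at the tail suit haemolysis.** If harm falls on a few patients with lower enzyme activity, the cut-off beats the mean, as the last table shows. This rules out replacing the cut-offs or ranking the mean above them. It does not argue against adding the mean.
- **Model detail belongs in an analysis plan that is not shown.** This holds for detail. But the protocol itself lists the outcomes and states a descriptive analysis, and the unequal windows follow from its own outcome wording and dosing table.

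**Conclusion.** The point holds as an improvement to a stated choice. The protocol names only yes/no haemoglobin outcomes, gives continuous haemoglobin as unadjusted summaries, and states no between-arm estimate for a regimen that doubles the daily dose.

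For a loss shared by most patients the cut-offs are the weaker tool: about 22-35% power against 90-99.8% for an extra 0.5 g/dL under the central assumptions. Those figures rest on inputs that the protocol does not supply. The ordering held across the grid, but it depends on a common shift and reverses when the loss is confined to a few patients.

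The unequal window needs no assumption beyond a literal reading of the two outcomes: two on-treatment readings in the 7-day arm against three in the 14-day arm, with day 7 counted only in the latter. That can favour the 7-day regimen.

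**What to change.** 1. Keep the three cut-offs as the clinical event outcomes. Assess the > 25% fall and the > 5 g/dL drop over the same window, days 1-14, in both arms.
2. Alongside them, prespecify a between-arm mean difference in haemoglobin with 95% CI, from a linear model adjusted for day-0 haemoglobin and site, for (a) the lowest value on days 1-14 and (b) the day-7 value.
3. State with the day-7 result that the 7-day arm has then finished dosing while the control arm is about halfway (7 of 14 doses over days 0-6), so it is not a comparison at equal cumulative dose. The lowest value on days 1-14 spans both courses.
4. Say in the plan that a mean can miss haemolysis confined to a few patients, so that the mean and the cut-offs are read together.

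The cost is revised outcome and analysis wording and a little more analysis work. No visit, sample or device changes, because every value is already scheduled in both arms.

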#### Interventions

This trial consists of two arms:Intervention arm: 0.50 mg/kg/day primaquine for 7 days (3.5 mg/kg total dose)Control arm: 0.25 mg/kg/day primaquine for 14 days (3.5 mg/kg total dose)

Additionally, all participants in both arms will receive blood schizonticide treatment, i.e. chloroquine (total dose 25 mg base/kg) as per NCVBDC guidelines [6, 7]. All chloroquine doses will be directly supervised.

All patients will be tested initially, and those found to be G6PD deficient (defined as < 30% of AMM) will be excluded from this randomised study but will receive medical care according to WHO guidelines: 0.75 mg/kg/week for 8 doses (total dose 6 mg/kg).

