### Participant timeline {13}

The participant timeline can be found in Table 1.

**Table 1 Tab1:** Study table

	Screening (Day − 1)	Enrolment (Day 0)	Day 1	Day 2	Day 3–6	Day 7	Day 8–13	Day 14	Day 21	Day 28	Month 2	Month 3	Month 4	Month 5	Month 6	Day of recurrence
Treatment																
CQ	X	X	X													
14 day PQ 0.25 mg/kg BW		X	X	X	X	X	X									
7 day arm PQ 0.50 mg/kg BW		X	X	X	X											
Procedures																
Malaria RDT for *P. vivax*	X															X
Dengue NS1 RDT	X															X
Physical examination including temp		X	X	X		X		X	X	X	X	X	X	X	X	X
CBC and LFT		X														X
G6PD UVS	X															
G6PD Biosensor	X															
Microscopy	X	X	X	X		X		X	X	X	X	X	X	X	X	X
Hb by Hemocue		X	X	X		X		X	X	X	X	X	X	X	X	X
Urine pregnancy test	X															X
Physical examination of urine			X	X		X										X
DBS		X														X
AE/SAE		X	X	X	X	X	X	X	X	X	X	X	X	X	X	X

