#### Study procedures for the main study

The screening process will be divided over the period of 2 days (Day − 1 and Day 0), and so will be the process of informed consent. This will be done to accommodate for potential delays in receiving the screening results for the G6PD testing. On Day − 1, a brief informed consent will be taken for initial screening tests and if the participant qualified for enrolment, written informed consent will be taken for enrolment into trial purposes. Detailed procedures are listed in Table 1.

Day − 1: All patients coming to the hospital with fever will be screened. For screening purposes, a brief informed consent will be taken and a venous blood sample will be collected. This will be used for malaria RDT, blood film microscopy, quantification of parasite density, dengue NS1 screening and G6PD testing. Women between the ages of 16 to 49 years willing to participate will be asked to take a urinary pregnancy test. A clinical checklist will be used to evaluate the exclusion criteria. Patients who test positive for vivax malaria will receive their first dose of chloroquine.

Day 0: Participants diagnosed with G6PD deficiency will be informed of their status and will be provided with information on the diagnosis and its consequences in everyday life and referred to a regular hospital clinician for treatment. Haemoglobin will be screened using Hemocue™ machine and patients who meet all enrolment criteria and are willing to provide written informed consent will be enrolled into the trial. Following enrolment, a questionnaire will be completed including demographic information, medical history, treatment history, history of recent blood transfusions, and a thorough physical examination will be performed. A venous blood sample will be taken for CBC and LFT. Dried blood spot (DBS) will be made and will be used for subsequent parasite analyses. All participants will receive the second dose of chloroquine under supervision. Patients in both the arms will receive their first dose of primaquine.

Day 1: All participants will be reviewed and the final dose of chloroquine treatment will be provided. Patients in both study arms will receive their second dose of primaquine. Finger prick blood sample will be collected for haemoglobin measurement and microscopy. Physical examination of urine will be conducted.

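### Two haemoglobin-fall endpoints are tied to the treatment period, so the scheduled day-7 reading counts in the 14-day arm but not in the 7-day arm

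*Protocol article*

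**What the plan says.** The Safety list under Outcomes {12} holds three haemoglobin endpoints:

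- a >25% "fall in haemoglobin on any day of treatment";
- an "acute drop in Hb of > 5 g/dL during primaquine treatment";
- "The incidence risk of anaemia (Hb < 8 g/dL) and/or the risk for blood transfusion", with no time limit in that list.

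The Abstract lists these outcomes too. Its only reference to the on-primaquine period comes at the end of the sentence, so it could govern the last item or the whole list.

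On dosing, the day 0 entry under Study procedures for the main study states: "Patients in both the arms will receive their first dose of primaquine". In Table 1 the row "7 day arm PQ 0.50 mg/kg BW" is marked at Enrolment, Day 1, Day 2 and Day 3–6, and is blank at Day 7. The 14-day row carries on through Day 7 and Day 8–13, and is blank at Day 14.

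On measurement, the Heamoglobin section (spelled so in the article) says "This will be done on days 0, 1, 2, 7, 14, 21, and 28", then monthly to month 6. Table 1 agrees: nothing is scheduled on days 3–6 or 8–13. The article neither sets a common window for the two arms nor extends the treatment period past the last dose.

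**The concern.** The window for two per-patient safety counts is set by the treatment under comparison. A patient whose fall first shows on day 7 is an event in the 14-day arm and a non-event in the 7-day arm. Day 7 is also the first scheduled reading after the whole short course, which is given at twice the daily dose.

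Safety of the 7-day course is a stated objective, and the article expects the results to inform national guidelines. The Background names haemolysis in G6PD-deficient patients as the serious hazard of primaquine, and the trial enrols down to 30% of the adjusted male median. If the counts are reported as defined, part of any apparent safety advantage of the short course could come from the window alone.

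**Working it through.** The plan gives no figure for this point, so there is none to reproduce. The check crosses each arm's dosing days with the haemoglobin schedule.

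**Step 1. Dosing days** (Interventions; Table 1; day 0 procedures). The first dose is on day 0 in both arms. Seven daily doses occupy days 0–6. Fourteen daily doses occupy days 0–13.

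**Step 2. Scheduled post-baseline readings** (Heamoglobin section; Table 1): days 1, 2, 7, 14, 21, 28, then monthly.

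**Step 3. Readings inside each arm's treatment period:**

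| | 7-day arm (days 0–6) | 14-day arm (days 0–13) |
|---|---|---|
| Day 1 | counts | counts |
| Day 2 | counts | counts |
| Day 7 | one day after last dose, does not count | counts |
| Day 14 | does not count | one day after last dose, does not count |
| Total counted | 2 | 3 |

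**Step 4. Exposure behind the last reading that counts** (doses taken × daily dose, out of 3.5 mg/kg).

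- 7-day arm, day 2: at most 3 × 0.50 = 1.5 mg/kg, and 1.5 / 3.5 = 43% of the course.
- 14-day arm, day 7: at most 8 × 0.25 = 2.0 mg/kg, and 2.0 / 3.5 = 57% of the course.
- At the shared day-2 reading the short-course arm has had more drug: 1.5 against 3 × 0.25 = 0.75 mg/kg. The gap lies in doses 4–7 of the short course, which no scheduled reading that counts can reflect.

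**Step 5. Illustration of size.** Let f be the share of the 7-day arm's falls first seen on day 7. Suppose all of the control arm's falls are seen by day 7. Then

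observed ratio (7-day / 14-day) = true ratio × (1 − f).

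The true risks and f are assumptions; the article gives none of them.

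| Assumed true risk, 7-day v 14-day | f = 25% | f = 50% | f = 75% |
|---|---|---|---|
| 5% v 5% (true ratio 1.0) | 0.75 | 0.50 | 0.25 |
| 10% v 5% (true ratio 2.0) | 1.5 | 1.0 | 0.5 |

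For example, with 5% in each arm and f = 50%, the 7-day arm shows 5% × 0.5 = 2.5%. Per 200 patients that is 5 against 10.

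**Step 6. The same with a common window.** Days 1–7 gives three scheduled readings in each arm (1, 2, 7). Days 1–14 gives four (1, 2, 7, 14).

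**The case against.** The strongest reply is that the wording is loose and that this reads it strictly. The two endpoints use two different phrases, and neither is defined as calendar days on which a dose is swallowed. A reading the day after a one-week course might be assigned to the treatment phase, and visit-window rules often sit in an analysis plan, which is not shown here. Part of this stands: a later rule could resolve the matter. But the article does state a window, its own Table 1 has no day-7 dose for the 7-day arm, and nothing in it brings day 7 inside. If day 7 is meant to count in both arms, the endpoint has to say so.

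Four further replies stand and limit the point.

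- A reader might infer that all the haemoglobin endpoints are affected. Only two of the three are: the Hb <8 g/dL or transfusion endpoint carries no treatment limit in the Safety list.
- A reader might infer that day-7 falls are concealed. They are not. Day-7 haemoglobin is collected in both arms, and the Safety analysis section summarises laboratory data by arm and visit, tabulates values beyond thresholds of concern, and summarises haematological adverse events. What is lost is the patient's place in two endpoint counts, which summaries by visit do not replace.
- A reader might infer that the short course is assessed on its first three doses alone. That is true of scheduled readings. Unscheduled visits and the CBC and LFT section provide blood counts prompted by symptoms, so a symptomatic fall on days 3–6 could be counted. Silent falls would not be.
- The control arm loses its own end-of-course reading, day 14, under the same strict reading. The net scheduled difference is one reading, 2 against 3.

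Finally, safety is summarised descriptively with no test or margin, and the efficacy conclusion is untouched.

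**Conclusion.** The point holds for the >25% fall and the >5 g/dL drop. As written, their window differs by arm: two scheduled readings count in the 7-day arm and three in the 14-day arm. The reading left out in the 7-day arm is the first that could reflect doses 4–7, so these endpoints can under-count falls there relative to control.

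How far they would do so cannot be determined, because the documents give neither the timing of the haemoglobin nadir nor a rate of falls. The ratios of 0.75, 0.50 and 0.25 show sensitivity under assumed equal risks. They ignore unscheduled readings and assume that no control falls first appear on day 14; such falls would offset part of the effect. A reader might go further and picture 0% against 5% from the window alone. That requires every fall in both arms to appear first on day 7, which nothing in the documents supports.

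This should be fixed before analysis. It does not threaten the primary efficacy result.

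**What to change.** Define both endpoints over one fixed calendar window counted from day 0, identical in both arms and including at least day 7, with the day 0 Hemocue value as the comparator. Possible wording: *any haemoglobin measured from day 1 to day 14 inclusive, in either arm, that is more than 25% (or more than 5 g/dL) below the day 0 Hemocue value*. Days 1–7 would also equalise the arms, with three scheduled readings each instead of four. Days 1–14 has the merit of including a reading after the full course in both arms. Use the same definition in the Abstract and in the Safety list, and say whether unscheduled readings count, by one rule for both arms.

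The cost is wording and notice of the amendment. All the samples are already scheduled, and no visit or treatment changes. The small downside is that the window takes in time off drug for the 7-day arm: one day with days 1–7, about a week with days 1–14. Recruitment has started and the trial is open-label, so the choice should be recorded before haemoglobin is compared by arm.
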